## Abstract

**Background:**

Literature shows that not only are traffic injuries due to accidents, but that there is also a correlation between different chronic conditions, the consumption of certain types of drugs, the intake of psychoactive substances and the self perception of risk (Health Belief Model) and the impact/incidence of traffic accidents. There are few studies on these aspects in primary health care.

The **objectives **of our study are:

Main aim: To outline the distribution of risk factors associated with Road Traffic Injuries (RTI) in a driving population assigned to a group of primary health care centres in Barcelona province.

Secondly, we aim to study the distribution of diverse risk factors related to the possibility of suffering an RTI according to age, sex and population groups, to assess the relationship between these same risk factors and self risk perception for suffering an RTI, and to outline the association between the number of risk factors and the history of reported collisions.

**Methods/Design:**

Design: Cross-sectional, multicentre study.

Setting: 25 urban health care centres.

Study population: Randomly selected sample of Spanish/Catalan speakers age 16 or above with a medical register in any of the 25 participating primary health care centres. N = 1540.

Unit of study: Basic unit of care, consisting of a general practitioner and a nurse, both of whom caring for the same population (1,500 to 2,000 people per unit).

Instruments of measurement: Data collection will be performed using a survey carried out by health professionals, who will use the clinical registers and the information reported by the patient during the visit to collect the baseline data: illnesses, medication intake, alcohol and psychoactive consumption, and self perception of risk.

**Discussion:**

We expect to obtain a risk profile of the subjects in relation to RTI in the primary health care field, and to create a group for a prospective follow-up.

**Trial Registration:**

Clinical Trials.gov Identifier: NCT00778440.

## Background

Traffic injuries are serious health problems that cause death, morbidity and disability, as well as an important impact on a country's economy [1]. There are three high risk groups: 15-24 years old who use mopeds or motorbikes, 18-34 years old driving as tourists, and over 65 years old pedestrians in urban areas. According to the last Catalan Health Survey (Enquesta de Salut a Catalunya ESCA) in 2006, 17.8% of those over 15 years of age had been injured in a road traffic accident (RTI) in the last year, 6.75% of whom had been injured in a road traffic collision in the previous two weeks. Figures for men were higher at 9.33% than for women at 4.33%. There were also differences in age with 8.05% aged between 15 and 44, 5.04% aged between 45 and 64 and 15.5% aged over 65 [2].

RTI are not coincidental, but they adhere to foreseeable factors. Medication and chronic conditions, despite not being the main implicated factors, are related to some cases [3-5]. Usually, when we talk about implicated factors in RTI, four groups can be considered: human factors, aspects related to the vehicle, aspects related to the collision environment (traffic, lane, etc) and socio-economic aspects [6,7].

The alcohol consumption factor on its own is the biggest contributor to the production of serious RTIs. The use of certain types of medication and psychoactive substances may alter the driving capacity as well [8]. In our field, between 5% and 15% of drivers killed in an accident show significant blood levels of other psychoactive substances (including or not including alcohol) [9]. There have also been international studies which have proven the existence of a relationship between psychoactive substances like benzodiazepines [10,11], cannabis and cocaine [12,13].

As for health problems, the previous morbidity of the driver is considered to be a possible accident inducing factor, and some chronic health problems like diabetes mellitus, epilepsy, hearing or visual impairments, cognitive deteriorations and some psychiatric disorders have been associated with RTI. Despite this, the illness-accident relationship is not easy to consider objectively due to methodological difficulties [14].

### Drugs and psychoactive substances

According to the 2006 Catalan Health Survey (ESCA'06), 21.7% of the Catalan population take some kind of medication, 69.5% of which is prescribed by a doctor, 5.5% prescribed by a pharmacist and 25% is self-medicated. Table 1 shows the available data on the consumption of certain medication which can affect driving capacities in the general population of Catalonia [2].

**Table 1 T1:** Consumption of certain drugs in the general population of Catalonia.

Pharmacological Group	General population (%)	Men (%)	Women (%)
Anxyolitics	9,1	5,72	12,38
Antidepressants	6,8	3,73	9,77
Antihistamines	3,18	2,44	3,89
Hypnotics	7,32	4,02	10,62
Antiepileptic drugs	0,3	0,28	0,30
Antiparkinsonian agents (>65 yrs)	0,76	0,6	0,8

ESCA'06

In a study carried out on the Spanish driving population killed in a traffic accident in 1992, 45% had been taking some kind of medication during the previous year, 17% of which were taken regularly [15].

On the other hand, a study which included 8,000 Spanish drivers showed that an estimated 10% of those killed or injured in a traffic collision had taken some kind of psychoactive substance. Moreover, an analysis by the National Toxicology Institute (Instituto Nacional de Toxicología) during the period between 1991 and 1999 showed that in 4.382 drivers killed on the road, 54% had taken some kind of psychoactive substance and 5% had been on medication [16,17]. Finally, a recent study, performed in Catalonia, which assessed subjects who had been injured in a traffic accident, observed a high prevalence of consumption of psychoactive substances, especially alcohol, cannabis and cocaine, which was relevant in all age groups [18].

Several review papers underline the effect of certain drugs on driving capacity such as narcoleptics or antipsychotics, anxyolitics, sedatives and hypnotics, tricycle antidepressants, lithium, (narcotic and non narcotic) analgesics and anti-migraine agents, anaesthetics, antiepileptic drugs, non steroid anti-inflammatory drugs, mio-relaxing agents, anti-Parkinson drugs, H1-antihistamines, anticolinergics and some cardiovascular drugs [19,20].

A recently published review paper suggests the need for research on the role of medication in road safety (other than the use of benzodiazepines, which has already been widely studied) [21], and the need to investigate more on the side effects of different drugs when driving [22].

In Spain, the cautionary information about the effect of drugs on driving capacities is ruled by Royal Law (Real Decreto) 1345/2007 [23], which newly includes a pictogram for any medication that can alter driving ability or the ability to use dangerous machinery. This information is currently being reviewed and classified according to the ICADTS (International Council on Alcohol, Drugs and Traffic Safety) categories, shown in Table 2. These take into consideration 3 groups according to the alcohol intake amounts considered safe, risky or not recommended. Currently, 424 active principles have been reviewed, which will lead to a change in 2,633 medicine labels by 2011, as in other eleven EU countries [24].

**Table 2 T2:** ICADTS classification of drugs in terms of driving effects

CATEGORY	DESCRIPTION	BAC (g/l)	ADVISE TO THE PATIENT
I	Presumed safe or unlikely effect	< 0,5	Read the patient information leaflet before driving.
II	Likely minor or moderate effect	0,5 - 0,8	Do not drive without consulting a health professional.
III	Likely severe effect or presumed dangerous	> 0,8	Do not drive while you are taking this medicine.

BAC: Blood Alcohol Concentration (g/l) equivalence.

The European Union has also dealt with problems related to medication and driving, particularly in an international project named "The Integrated Project DRUID (Driving Under the Influence of Drugs, Alcohol and Medicines)", which analyses the effect that the intake of medicines, medicinal herbs and psychoactive substances can have on road safety [25].

### Chronic health conditions

Until the 1960's, the correlation between chronic health problems and road traffic injuries was very controversial. Different groups of researchers started to observe a correlation between collisions and injuries suffered by drivers with diabetes, epilepsy, cardiovascular illnesses, alcoholism and mental disorders [26].

Some ongoing studies are currently studying the effect that diverse long-term conditions and age, elements that usually go together, can have on the incidence of RTIs [27].

The Catalan Accident Statistics Annual Report (2003) indicates that in 7.6% of the collisions with victims, drivers suffered from the sudden appearance of an illness [28]. This same observation has been suggested at an international level [29]. According to data obtained from diverse review papers [30-33], a risk table has been published for different health problems and their adjusted risk, if the correct treatment was carried out. The following findings should be noted: the relative risk of a driver with a chronic health condition of suffering a traffic injury is 1.33 (IC95% 1.28-1.37); the most highly associated illnesses are: Sleep Apnea Syndrome [RR 3.71 (IC95% 2.14-6.4)], neurological conditions [RR 1.75 (IC95% 1.61-1.89)], arthritis/joint limitations [RR 1.17 (IC95% 1.004-1.36)], cardio-vascular illnesses [RR 1.23 (IC95% 1.09-1.38)], diabetes mellitus [RR 1.56 (IC95% 1.31-1.86)], mental disorders [RR 1.72 (IC95% 1.48-1.99)], visual impairments [RR 1.09 (IC95% 1.04-1.15)], hearing impairments [RR 1.19 (IC95% 1.02-1.4)] and high alcohol consumption [RR 2.00 (IC95% 1.89-2.12)] [30].; and the risks for the population with chronic health problems diminish in general if they are being treated and adequately controlled, with the exception of some chronic health problems where the risk can increase through the use of different types of medication (e.g. benzodiazepines) [31,34].

### The situation in Primary Care

In our country, few articles have been published on RTI and their impact in Primary Health care. Most of them, written during the 1990's have consisted of descriptive epidemiological studies on the impact of road traffic injuries on the number of emergency consultations, its prevalence according to age groups and gender and studies on time, place and gravity of the RTI. If summarised, they show that the frequency of RTI is approximately 8 per 1,000 inhabitants [35,36] making up 4.1% of all consultations in a primary health care centre [37]. Of all collision accidents of any kind, those on a public road are the second most frequent, after domestic accidents, road traffic injuries making up between 8.3% and 8.6% of all kinds [37-39].

The most serious RTI happen on the road, and affect male drivers more (approximately 70%), with an average age of 27 ± 3 years [35-37], with a large peak in the group around 20 ± 5 years of age (42.8% of cases) [36]. The impact makes up 1% of the total of patients attended in an emergency centre [40].

Diverse authors warn of the high occurrence of RTI in children (245 per 1,000 inhabitants) [38], and the importance of the use of child protection methods in vehicles. 20.75% of child accidents correspond to the RTI that affect those aged 12 ± 2 years [41,42].

### The Theory of Change model and risk of RTI

There are different theoretical explanations which try to predict the change in the prevention behaviour of populations. Of all the analysed theories [43], the so called Health Belief Model shows that the most important elements are: risk perceptions (personal susceptibility to suffer an injury), capacity to carry out effective activities and their economic costs.

Several studies have aimed at describing the risk perception in relation to risky driving behaviours [44], cultural differences [45], the use of mobile phones while driving [46], the position of hands when driving [47]. Diverse population groups have also been studied such as young drivers compared to older drivers [48]. Others have examined differences in the perception of traffic risks for older and younger adults [49]. Also, the perception of risk has been studied in relation to training [50], age and driving expertise [51]. These have been particularly assessed amongst drivers under the effects of alcohol [52,53]. Just a few studies have established the existing relationship between health conditions and risk perception; amongst them, we found some papers on risk perception in diabetic patients during hypoglycaemic stages [54,55], and in epileptic subjects [56].

Available publications show several methods to measure the risk perception for an RTI. Likert scales with closed questions and a scale between complete disagreement to complete agreement have been used in some cases [47], as well as multiple-choice questionnaires (measuring probability of traffic accidents, consequences of traffic accidents, risk sensitivity and risk willingness with Likert scales) [45]. In some studies, the risk associated to particular traffic conditions and driving behaviours was assessed [50] and in others it was analysed with questions with three options; low, medium and high risk [44]

### Justification For The Study

The available research in this field has been revised and a consensus that included recommendations to carry out epidemiological studies in different areas provided. Given the current situation, studies that inform us of the situation at a level closest to the patient (primary health care) are essential. As are studies that permit us to set out risk levels based on a description of exposition to drugs, riskful behaviour (alcohol intake and consumption of other psychoactive substances) and chronic and acute health conditions, and studies that assess the RTI risk perception of drivers.

On the other hand, the prospective group follow-up can give us an idea of the changes that may appear in terms of RTI risk factors, and in terms of traffic collisions with/without injuries. Without a doubt, this is useful information in the planning of preventative interventions in primary health care.

## Objectives

Main aim: to assess the distribution of the risk factors associated with RTI in a driving population assigned to a group of participating primary health care centres in the city of Barcelona.

Secondary objectives: 1. To study the distribution of RTI risk factors relative to medications, illnesses, alcohol intake and/or consumption of psychoactive substances in the driving population in different groups according to age and gender. 2. To outline the correlation between the number of risk factors related to suffering an RTI and the background of registered collisions, having or not having recieved medical attention. 3. To assess the existing relationship between the self perception level of risk of RTI and the presence of chronic health conditions, medication or consumption of psychoactive substances.

## Methods/Design

### Study design

Cross-sectional and multicentre study.

### Setting

25 primary health care centres in Barcelona.

### Study population

Drivers aged 16 or above who have been attended and who have a clinical register at the participating primary health care centres.

### Sample size calculation

The calculation was carried out using the population of men and women with a driving license in the Barcelona province from the age 16 and over, according to the 2005 census of drivers made available by the General Traffic Department (DGT). For sample calculation purposes, four age groups proportional to women and men were created. Accepting an alpha risk of 0.05 with a precision of +/- 0.05 percentage units in a bilateral contrast for an estimated proportion of 0.5, a random population sample of 385 subjects was determined for each age group. The total sample size is 1540 subjects (Table 3).

**Table 3 T3:** Sample size according to the estimated distribution in age and gender groups

	16-24 yrs	25-34 yrs	35-64 yrs	Above 74 yrs	Total
Men	214	212	228	317	971
Women	171	173	157	68	569

Total	385	385	385	385	1540

### Recruitment Process

The study population will be recruited by consecutive sampling. Each collaborating researcher, after verifying the inclusion criteria, will include 16 subjects, two for every age and gender group of those described in the table above. All subjects of 16 years of age or over that consult any collaborating health professionals (nurses or doctors) for any motive, will be invited to participate. They will be informed by the collaborating researcher (patient information leaflet) and asked to take part in the study and in yearly follow-ups via telephone. In case of acceptance, they will read and sign a consent form. Each centre will recruit patients until reaching the number of participants stipulated, taking into account the necessary distribution by age groups and sex. Figure 1 Flow Chart: Algorithm of the study shows the recruitment system and yearly monitoring.

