## Discussion

There are various motives that justify the importance of this study. Primary health care is an advantageous location to carry out preventive interventions in RTI. In our country, according to data provided by the Primary Health Care Information System, 75% of the population consults a general practitioner at least in their life, and the average number of visits is between 5 and 6 yearly. Furthermore, public health cover in Spain is practically universal. This makes primary health care an ideal place for the study and implementation of preventive measures in the RTI field. These could include warnings from the side effects of certain medication, the effects of psychoactive substances on driving skills to the importance of the control and monitoring of chronic or acute illnesses that help the patient elaborate a real reception of their physical state and capacity to drive [60-62].

RTI pose health problems that are extremely high in magnitude and in social and health repercussions. The Catalan Public Health Plan contemplates this intervention as a priority objective, and so establishes the following main aims for 2010: 1. To reduce by 20% the mortality rate associated with RTI in the main 3 population groups where they are most frequent (see introduction). 2. To reduce by 50% the mortality rate associated with RTI in men and women from 15 to 24 years old. 3. To reduce by 50% the mortality rates associated with RTI in drivers linked to an excessive intake of alcohol. 4. To reduce by 25% the prevalence of severe injuries associated with RTI in the 3 main population groups (see introduction).

The elements evaluated in this study (medication, chronic health conditions, consumption of psychoactive substances), are often managed in the Primary Care field and are therefore registered in medical records. Moreover, these are aspects that are inherently related to the Primary Health Care field which means that the date is quite complete and difficult to attain in other existing registers.

The improvement in the basic knowledge of risk levels of suffering from an RTI that this study aims to achieve is a necessary first step for the definition of preventative activities in primary health care in the near future.

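### The sample is described as random, but recruitment takes consecutive consulting patients to quotas, so prevalence of illness and medication may be overstated by an amount that the ±5-point precision does not cover

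*Protocol article*

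**What the plan says.** The Protocol article describes its sampling in two ways.

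- Abstract, Methods/Design: "Randomly selected sample of Spanish/Catalan speakers age 16 or above with a medical register in any of the 25 participating primary health care centres".
- Sample size calculation: "a random population sample of 385 subjects was determined for each age group".
- Recruitment Process: "The study population will be recruited by consecutive sampling". Each collaborating researcher "will include 16 subjects, two for every age and gender group of those described in the table above". The same section says "All subjects of 16 years of age or over that consult any collaborating health professionals (nurses or doctors) for any motive, will be invited to" take part.

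The target population is also given twice. Under Objectives, the main aim is "to assess the distribution of the risk factors associated with RTI in a driving population assigned to a group of participating primary health care centres". Under Study population it is narrower: drivers who have already been seen at a participating centre and have a record there.

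The Statistical analysis section promises 95% confidence intervals for the descriptive results. The section on difficulties and limitations restricts generalisation to an urban population and says nothing about selection through attendance.

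**The concern.** A draw from the register gives every registered driver in a stratum the same chance of selection. Taking whoever consults until a quota fills does not: people who come often are more likely to be among the first arrivals, and people who do not come cannot enter. The two descriptions cannot both be true.

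This matters because the main aim is itself a description of prevalence, and some of the factors described (chronic conditions, long-term and recent medication) are reasons for consulting. For those factors, selection depends on the quantity being estimated. The resulting error is not part of the confidence interval and does not shrink with a larger sample.

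**Working it through.** **1. The plan's own figure.** Inputs from Sample size calculation: two-sided alpha 0.05, expected proportion 0.5, precision 0.05 (read as five percentage points, which is what reproduces the result).

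n = z² × p(1 − p) / d² = 3.84146 × 0.25 / 0.0025 = 384.15, rounded up to 385. Four age groups give 4 × 385 = 1540.

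Both stated figures reproduce. The formula assumes a simple random sample within each group, which the recruitment rule does not deliver.

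**2. How selection works under the quota rule.** The Abstract gives 1,500 to 2,000 people per care unit. The Discussion says that "the average number of visits is between 5 and 6 yearly". If that average applies to a unit's list, the unit sees between 1,500 × 5 = 7,500 and 2,000 × 6 = 12,000 visits a year. One researcher's 16 places are 16/2,000 = 0.8% to 16/1,500 = 1.1% of the list. Filling so few places with the first eligible arrivals makes inclusion roughly proportional to visit frequency within each cell. The exception is a cell so small that most of its eligible drivers are needed.

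**3. Effect on prevalence.** Let p be the true prevalence in a cell and k the ratio of consultation rates, with versus without the factor, in that cell. The expected sample prevalence is

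q = pk / (pk + 1 − p).

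The document gives no k, so 1.25 to 2 is an assumed range. The prevalences 21.7% (any medication) and 9.1% (anxiolytics) are the general-population survey figures in the Background, used as illustrations. 50% is the planning value.

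| True p | k = 1.25 | k = 1.5 | k = 2 |
|---|---|---|---|
| 9.1% | 11.1% | 13.1% | 16.7% |
| 21.7% | 25.7% | 29.4% | 35.7% |
| 50% | 55.6% | 60.0% | 66.7% |

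Example: 0.217 × 2 / (0.434 + 0.783) = 0.434 / 1.217 = 35.7%.

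At 21.7% the excess is 4.0, 7.7 and 14.0 points. It reaches five points when k equals the odds at 26.7% divided by the odds at 21.7%: 0.3643 / 0.2771 = 1.31.

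**4. Effect on the interval.** With n = 385 and a true 21.7%, the standard error at k = 1.25 is √(0.2573 × 0.7427 / 385) = 0.0223. The shift is 0.0403 / 0.0223 = 1.81 standard errors. By the normal approximation the nominal 95% interval covers the true value about 56% of the time. At k = 1.5 the same steps give about 9%.

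**5. Would weighting help?** Suppose visits are Poisson with yearly rate λ, and the count for the previous 12 months includes the index visit. Its expected inverse is then (1 − e^−λ)/λ. Multiplied by visit-proportional inclusion, this recovers drivers with at least one visit a year. With a mean of 5.5 visits, k = 2 and p = 21.7%, the rates are 5.5 / 1.217 = 4.52 without the factor and 9.04 with it. The weighted prevalence is 0.217 × 0.9999 / (0.217 × 0.9999 + 0.783 × 0.9891) = 21.9%, against 35.7% unweighted.

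**The case against.** The strongest reply has four parts.

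*The population is already limited to attenders.* Study population names drivers who have been seen, so excluding those who never consult is partly declared. This stands. It does not settle the matter: the main aim still refers to assigned drivers, and among attenders the frequent ones are still over-represented.

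*The Sample size wording may only state the formula's usual assumption.* That is fair, and the Abstract is the plainer contradiction. Still, a reader of either section would take the sample to be random.

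*The bias fades if recruitment stays open long enough.* If the sample were drawn from everyone seen in a window of T years, the expected prevalence would be p(1 − e^(−λ₁T)) / [p(1 − e^(−λ₁T)) + (1 − p)(1 − e^(−λ₀T))], where λ₁ and λ₀ are the yearly rates with and without the factor. With k = 2 and 5.5 visits a year, 21.7% would read 26.8% over 3 months and 21.9% over 12 months. Inverse-rate weights would then over-correct: at 3 months, 0.134 / (0.134 + 0.732) = 15.5%, an error of −6.2 points against +5.1 unweighted. No recruitment duration is given. The planned rule, however, fills a few places per cell with the first arrivals and stops, so most of this objection falls. What remains is a reason to keep weighting as a sensitivity analysis.

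*The size and sign are not established.* This stands in part. A reader might infer that the prevalence of every risk factor is overstated by a known amount. The document does not support that: it gives no visit ratios and no reason to expect drinkers or substance users to consult more often. The quotas also remove the part of the bias that comes from age and sex, and the exclusion of terminal illness, serious psychiatric problems and disabling conditions may pull the other way.

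**Conclusion.** The contradiction is explicit and bears on the main aim: two places present the sample as random, and the recruitment rule makes it a consecutive quota sample of people who consult. The sample-size arithmetic is correct, but its ±5 points describes random error in a design that is not the one planned.

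For chronic illness and medication an upward bias is plausible. Under assumed within-cell visit ratios of 1.25 to 2, a true 21.7% would read about 26% to 36%. The excess passes the planned precision once the ratio exceeds about 1.31. For alcohol and psychoactive substances no direction can be stated. These sizes rest on the assumed ratios and on selection by first arrival. They show what the design allows and are not estimates of what will happen.

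**What to change.** - In the Abstract and the Sample size calculation, replace the random-sample wording with *consecutive quota sample of consulting drivers*.
- Reconcile Objectives (assigned drivers) with Study population (attended drivers), and restrict the main-aim conclusion to consulting drivers.
- State that the ±5-point precision excludes selection error.
- Add attendance-related selection to the limitations: upward bias is plausible for illness and medication, and the direction is unknown for alcohol and psychoactive substances.
- As a sensitivity analysis, record each participant's consultations in the previous 12 months, counting the index visit, and report prevalences weighted by the inverse of that count beside the raw ones. Counting the index visit keeps the weight defined for first-time visitors. Where no record is open, which the limitations section expects for some participants, ask the patient.

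The first four items cost only wording. The last costs one extra data field and gives wider intervals. It depends on the quality of the visit count and on selection by first arrival, and it cannot recover drivers who do not consult.

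### The per-researcher quota of two subjects per age-and-gender cell forces a 1:1 sex split and contradicts the census-proportional split of Table 3; the effect is material mainly in the oldest age group

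*Protocol article*

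**What the plan says.** In the Sample size calculation section, the starting point is the 2005 census of licensed drivers in Barcelona province, from which "four age groups proportional to women and men were created". The precision statement reads "Accepting an alpha risk of 0.05 with a precision of +/- 0.05 percentage units in a bilateral contrast for an estimated proportion of 0.5", and from it "a random population sample of 385 subjects was determined for each age group". Table 3 then fixes eight cells across the four age groups: men 214, 212, 228 and 317 (971 in all), women 171, 173, 157 and 68 (569 in all).

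The Recruitment Process section sets the working quota. Each collaborating researcher "will include 16 subjects, two for every age and gender group of those described in the table above", which refers back to Table 3. The same section adds that each centre recruits up to a stipulated number, "taking into account the necessary distribution by age groups and sex". It gives no cell counts for this and does not say which instruction prevails.

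The Statistical analysis section reports descriptive results with 95% confidence intervals and mentions no weighting by sex.

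**The concern.** Two subjects in each of eight cells is a 1:1 sex allocation within every age group. Table 3 is not 1:1 in any age group, and in the oldest it is more than four men to one woman (317 to 68). A researcher who follows the quota and a centre that works to Table 3 would enrol different samples.

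The main aim is to describe how risk factors are distributed in a driving population, and precision is claimed for each age group. If a factor differs between men and women, the unweighted prevalence in an age group depends on the sex mix recruited. Several of the drug groups in the article's own Table 1 differ markedly by sex, so the choice between the two allocations can change the reported figures.

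**Working it through.** **Inputs.** From the Sample size calculation section: two-sided alpha 0.05, expected proportion 0.5, half-width 0.05 (read as 5 percentage points), and the Table 3 counts. From the Recruitment Process section: 16 subjects per researcher, two per cell. From Table 1: anxiolytic use 5.72% in men and 12.38% in women.

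**1. The plan's own figure.** n = 1.96² × 0.5 × 0.5 / 0.05² = 384.15, rounded up to 385; 4 × 385 = 1540. Both reproduce. The rows and columns of Table 3 also add up (971 + 569 = 1540; every age column 385).

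**2. What the quota delivers.** 4 age groups × 2 sexes × 2 = 16 per researcher. 1540 / 16 = 96.25 researchers.
- 96 researchers: 192 per cell, 384 per age group, 768 men and 768 women, total 1536.
- 97 researchers: 194 per cell, 388 per age group, 776 men and 776 women, total 1552.

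**3. Comparison with Table 3 (97 researchers).**

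| | 16-24 | 25-34 | 35-64 | Oldest |
|---|---|---|---|---|
| Men, Table 3 | 214 | 212 | 228 | 317 |
| Men, quota minus Table 3 | -20 | -18 | -34 | -123 |
| Women, Table 3 | 171 | 173 | 157 | 68 |
| Women, quota minus Table 3 | +23 | +21 | +37 | +126 |
| Share of men, Table 3 | 55.6% | 55.1% | 59.2% | 82.3% |
| Share of men, quota | 50% | 50% | 50% | 50% |

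At two per researcher, 317 older men need 317 / 2, so 159 researchers, while 68 older women need 34. No single number of researchers satisfies both. Matching Table 3 would take an average per researcher of 16 × cell / 1540: men 2.22, 2.20, 2.37 and 3.29; women 1.78, 1.80, 1.63 and 0.71.

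**4. Shift in an unweighted age-group prevalence.** Shift = (Table 3 share of men - 0.5) × (rate in women - rate in men). For anxiolytics the sex difference is 12.38 - 5.72 = 6.66 points.
- Oldest group: 0.3234 × 6.66 = 2.15 points. The quota gives (5.72 + 12.38) / 2 = 9.05%; the Table 3 mix gives 0.823 × 5.72 + 0.177 × 12.38 = 6.90%.
- Other groups: 0.0558, 0.0506 and 0.0922 × 6.66 = 0.37, 0.34 and 0.61 points.

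**5. Cost of weighting the quota sample back to Table 3.** With equal cells, design effect = 2 × (share of men² + share of women²), and half-width = 1.96 × √(0.25 × design effect / 385) at p = 0.5.
- Oldest group: 2 × (0.823² + 0.177²) = 1.42, effective n about 272, half-width about 5.9 points.
- Other groups: design effects 1.01, 1.01 and 1.03, half-widths 5.0 to 5.1 points.

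**6. Precision for oldest women alone, p = 0.5.** 1.96 × √(0.25 / 68) = 11.9 points with the Table 3 count; 1.96 × √(0.25 / 192) = 7.1 points with equal cells.

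**The case against.** The strongest reply is that the precision target is 385 per age group, and the quota meets it to within a few subjects. That stands. A reader might infer that the sample size as a whole is undeliverable; steps 1 and 2 show that only the sex split within age groups fails. Estimates reported separately for men and women, which the first secondary objective needs, are not distorted.

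A second reply is that the centre-level sentence points to the Table 3 distribution, and if it governs, Table 3 can be reached. This is fair, and the recruitment flow chart, which could not be seen, may say more. But the text gives no cell counts for centres and does not override the two-per-cell rule, so the two instructions still conflict.

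Third, sex is recorded, so weighting can remove the shift, and an analysis plan that is not shown may specify it. The absence of weighting from the article is therefore no fault in itself. An analysis plan cannot, however, make two recruitment targets agree.

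Fourth, the illustration is a marked case. Antihistamines would shift by about 0.5 point in the oldest group (0.3234 × (3.89 - 2.44)), and antiepileptics by less than 0.01 point (0.3234 × (0.30 - 0.28)). Even the anxiolytic shift of 2.15 points is below the sampling half-width of about 2.5 points at n = 385 (1.96 × √(0.069 × 0.931 / 385)). This limits the size of the problem; it does not remove a systematic shift.

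Finally, equal cells are a legitimate design with a real advantage for older women (step 6).

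**Conclusion.** The contradiction stands. The quota implies 50% men in every age group, Table 3 implies 55.6%, 55.1%, 59.2% and 82.3%, and nothing in the article says which applies. Followed as written, the quota would enrol about 192 to 194 oldest women against 68 planned, and as many oldest men against 317.

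The material effect is confined to unweighted estimates and mainly to the oldest group, where anxiolytic use would read 9.05% against 6.90%. This assumes that Table 1's all-age, general-population rates apply to the oldest drivers, which the article does not establish, so the figure is illustrative only.

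A reader might also infer that the ±5 points is lost in general. It is not. After weighting, the 5.9 points in the oldest group is a worst case at p = 0.5. With the design effect of 1.42, ±5 still holds while p(1 - p) is at most 0.0025 × 385 / (1.96² × 1.42), about 0.18, that is, for prevalences below about 23% or above about 77%. All the drug rates in Table 1 lie in that range. The calculation takes the Table 3 proportions as the 2005 census shares.

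**What to change.** Reconcile the Sample size calculation and Recruitment Process sections in one of two ways, and state which was chosen.

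(a) Replace the two-per-cell rule with study-wide cell targets equal to the Table 3 counts, allocated across centres so that the cells sum exactly to Table 3. Dividing by 25 and rounding alike everywhere will not do this: in the 35-64 group, 228 / 25 = 9.12 and 157 / 25 = 6.28, and rounding to 9 and 6 gives 25 × 15 = 375, not 385. It would also presume centres of equal size, which the article does not state. The price of this option is that 68 oldest women support only about ±12 points for that cell.

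(b) Keep two per cell and replace the Table 3 counts with about 192 to 193 per cell (1540 / 8 = 192.5). Compute each age-group estimate as a sex-weighted mean using the 2005 census shares, and restate the worst-case precision (p = 0.5) as about ±6 points in the oldest group and ±5.0 to 5.1 in the others. The price is the wider interval in the oldest group; the gain is better precision for older women.

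Either option costs a short change to the text and a revised quota sheet or table, plus a line on weighting under (b). Neither needs additional patients. If subjects have already been enrolled under the two-per-cell rule, (b) is the practical choice.
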